### Data management and monitoring

The protocol will not be initiated until it has received full approval by the relevant IRBs at each study site. All research staff that regularly come in contact with study participants will be instructed on procedures for managing and reporting adverse events. All adverse events will be documented, and records regarding the events will be retained for review by the study team. The VCU investigator will be informed immediately, in person or by telephone, of any potential or actual unanticipated problems at VCU, and they will report all unanticipated problems to the IRB at VCU within 5 days. VCU will also report unanticipated problems that occur at PSU to the VCU IRB within 5 days of becoming aware of the problem.

The study will be monitored by a Data and Safety Monitoring Board (DSMB) established at VCU and composed of four scientists not otherwise affiliated with the clinical trial. They will have expertise in substance abuse, psychiatric co-morbidities and biostatistics. The DSMB will meet (in person or via tele/video conference) once prior to the start of the study and at least semi-annually. Prior to the start of the study, the DSMB will establish a charter including study stopping rules and unblinding rules and procedures.

The Study Coordinator will generate a semi-annual report of aggregate data (including data collected at VCU and PSU) to be circulated to the PIs, project Co-investigators, and the four DSMB members. The report will summarize rates of recruitment, participants’ demographic characteristics, adverse events, unanticipated problems, serious adverse events (as defined the FDA), participant drop-out rates, cigarettes smoked per day, study product used per day, and expired air CO levels, and protocol deviations/violations. DSMB members will have one week to review the semi-annual report materials and either recommend that recruitment continue as planned or request a face-to-face meeting of the PI, the Study Coordinator, and all four DSMB members. If a DSMB meeting is convened, members will be asked to decide whether the study should: a) proceed as planned; b) proceed, but with a protocol amendment; or c) discontinue recruitment pending further investigation. If one or more DSMB members select option b or c, the PIs will inform their respective IRBs of such in a written report that is also copied to the FDA. Finally, a copy of the aggregate data report will be provided annually to the VCU and PSU IRBs.

Data security will be insured as follows. The majority of participant data will be collected using REDCap [50], a secure web application for collecting and storing research data hosted at VCU and made available through a collaboration between the VCU Center for Clinical and Translational Research and VCU Technology Services. To protect confidentiality, each participant will be assigned a participant ID number that will be used to identify all biological specimens. This unique participant ID number will also appear in the REDCap database associated with all data collected electronically.

### Statistical analysis

The analysis plan is based on the primary objective of determining the extent to which ECIG nicotine concentration influences NNK exposure as indexed by urinary NNAL concentration. We will first examine baseline characteristics including demographics and smoking history across study interventions to identify any baseline imbalances after randomization. Discrete variables will be summarized by frequencies and percentages and compared using Chi-squared test or Fisher’s exact test. Continuous covariates will be summarized by mean, standard deviation, median and range, and compared by one-way ANOVA. Skewed continuous variables will be log-transformed or square root transformed as appropriate. We expect groups to be balanced for important baseline characteristics due to randomization. A secondary analysis will be completed adjusting for age, gender, and race, along with any other covariates that differ across research interventions at baseline with a p-value less than 0.20. P-values less than 0.05 will be considered statistically significant with the exception of analysis of our primary analysis, where p-values less than 0.008 will be considered significant after a Bonferroni multiple comparisons adjustment. Our primary endpoint, urine NNAL concentration, will be summarized by study intervention and time and analyzed using linear regression, and we will adjust the Type I error rate to account for 6 pairwise comparisons at each time point. We will compare each ECIG group to the cigarette substitute and then each ECIG group to the other. An analogous approach will be used to analyze our secondary endpoints. The primary analysis of our secondary endpoints will use linear regression. Secondary analyses will consist of an adjusted analysis and a repeated measures analysis using a linear mixed model. All analysis will be completed using SAS (v.9.4) under the expertise of a senior biostatistician.

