
### Aim

The specific aims of the RCT are to:*Characterize ECIG influence on toxicants*, *biomarkers, health indicators, and disease risk.* We will measure exposure to the carcinogenic nitrosamine 4-(methylnitrosamino)-1-(3-pyridyl)-1-butanone [NNK; via its metabolite NNAL (4-(methylnitrosamino)-1-(3-pyridyl)-1-butanol) in urine], expired air carbon monoxide (CO), and nicotine (via its metabolite cotinine in urine). We will also measure heart rate and blood pressure, biochemical and hematologic health indices, pulmonary function (via spirometry), and biomarkers of oxidative stress. With respect to toxicant exposure, we hypothesize that, relative to the cigarette substitute condition, we will observe ECIG liquid nicotine concentration-related decreases in urine NNAL and expired air CO concentration.*Determine the tobacco abstinence symptom and adverse event profile associated with real-world ECIG use*. We will use standard measures of nicotine/tobacco abstinence symptoms to characterize the extent to which ECIG-induced suppression of abstinence symptoms is related to nicotine concentration. With respect to other adverse events, we will assess effects likely attributable to inhalation of propylene glycol and nicotine self-administration. We hypothesize more of these propylene glycol-related adverse events with ECIGs relative to the cigarette substitute condition.*Examine the influence of ECIG use on conventional tobacco product use.* We will monitor ECIG and all other tobacco/nicotine product use closely, via daily tobacco use diaries and in-person assessments. Because we are targeting individuals interested in reducing their cigarette intake, we hypothesize that individuals randomized to higher ECIG nicotine concentrations (8 mg/ml or 36 mg/ml) will experience reductions in combustible cigarette use.

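### Bonferroni for the six pairwise NNAL comparisons is valid but needlessly conservative; Holm's step-down gains 2 to 5 points of power on a true pair at the same familywise error

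*Protocol article*

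**What the plan says.** The Statistical analysis section of the protocol article opens with its objective: "The analysis plan is based on the primary objective of determining the extent to which ECIG nicotine concentration influences NNK exposure". Urinary NNAL is analysed by linear regression, and "we will adjust the Type I error rate to account for 6 pairwise comparisons at each time point". The pairs are named: "We will compare each ECIG group to the cigarette substitute and then each ECIG group to the other". That makes three ECIG-versus-substitute and three ECIG-versus-ECIG comparisons. The threshold is fixed too: "p-values less than 0.008 will be considered significant after a Bonferroni multiple comparisons adjustment". Beyond the pairwise tests, "Secondary analyses will consist of an adjusted analysis and a repeated measures analysis using a linear mixed model".

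The Aim section states the NNAL hypothesis with its comparator: "relative to the cigarette substitute condition, we will observe ECIG liquid nicotine concentration-related decreases in urine NNAL".

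**The concern.** The article fixes the adjustment method, the number of comparisons and the threshold, so this is a stated choice and not a detail left to an analysis plan that is not shown. Single-step Bonferroni holds every comparison to 0.05/6, even after other comparisons in the family have been rejected. Holm's procedure relaxes the threshold after each rejection and still controls the familywise error under any dependence among the tests. Keeping the single-step rule therefore gives up some power on true differences and buys no extra protection beyond 0.05. This matters a little more here because a two-sided test at 0.008 has less power than the 80% given in the Sample size section.

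**Working it through.** **Inputs.** From Sample size: 100 completers per condition, difference 0.28 pmol/ml, SD 0.6 pmol/ml, stated power 80%. From Statistical analysis: six comparisons, each at 0.008. From Randomization: 1:1:1:1 allocation. Sidedness is not stated; I assume two-sided.

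**Plan's own figure.** Noncentrality = 0.28 / (0.6 × √(2/100)) = 0.28 / 0.0849 = 3.30. Power ≈ Φ(3.30 − z).

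- Two-sided 0.008: z = 2.652, Φ(0.648) = 74%.
- Two-sided 0.05/6: 75%.
- One-sided 0.008: 81%.
- Two-sided 0.05/3: 82%.
- Two-sided 0.05: 91%.

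So 80% can be reached under some readings, but not with a two-sided test at the threshold in the Statistical analysis section. The exact t calculation with pooled variance (396 df) gives 73.7% at 0.008, and that is the baseline below.

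**Thresholds.** Bonferroni uses 0.05/6 = 0.0083, rounded to 0.008, for every pair. Holm orders the six p-values and compares them in turn with 0.05/6 = 0.0083, 0.05/5 = 0.0100, 0.05/4 = 0.0125, 0.05/3 = 0.0167, 0.05/2 = 0.025 and 0.05, stopping at the first failure. No threshold is below Bonferroni's and the first is identical. Hence Holm never rejects less, and the chance of at least one rejection equals that of Bonferroni at 0.05/6.

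**Simulation.** 200,000 four-arm trials per pattern, 100 per arm, SD 0.6, pooled t with 396 df. The response patterns are assumptions: the 36-versus-0 difference is 0.28 and the substitute mean equals the 0 mg/ml mean.

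| Pattern over 0/8/36 mg/ml | Power 36 vs 0, Bonferroni 0.008 | Power 36 vs 0, Holm |
|---|---|---|
| Linear in concentration | 73.6% | 76.2% |
| Equal steps | 73.7% | 76.2% |
| Effect only at 36 | 73.7% | 77.0% |
| Plateau from 8 | 73.5% | 78.8% |

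If instead all four arms differ, falling in three equal steps from the substitute to 36 mg/ml with 0.28 overall, the 36-versus-substitute pair goes only from 73.7% to 75.1%. Simulated familywise error under Holm was about 4% with no true differences and lower in the other patterns.

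**Trend contrast over the three ECIG arms, scored 0/8/36.** Two-sided at 0.05: 93% if linear in concentration, 88% for equal steps, 96% if only 36 mg/ml works, 72% for a plateau from 8 mg/ml, and 21% if only 8 mg/ml works. At an equal alpha of 0.008 with a linear response it has 78.8%, against 73.6% for the pair. The pair alone has 91% at 0.05, so most of the step from 74% to 93% comes from the looser alpha.

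Placed in a seven-test Holm family, the trend has 79%, 71%, 54% and 86% power for linear, equal-step, plateau and 36-only patterns. The planned comparisons already reject at least one ECIG-versus-ECIG pair in 79%, 76%, 87% and 87%. Added at 0.05 beside the Holm tests with no gate, the trend raises global-null familywise error to about 7.5%.

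**The case against.** The strongest reply is that nothing here is an error. The Bonferroni plan is pre-specified, controls the familywise error and is arithmetically consistent, since 0.05/6 is about 0.008. Holm's gain is small. It also cannot help a trial in which every pair misses the threshold, because its first step is the same 0.05/6. All of this stands. It limits the point to a modest improvement but does not remove it, because the improvement carries no price in error rate or assumptions.

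A reader might infer something stronger: that the objective is an ordered concentration effect, that six unordered pairs fail to test it, and that one trend contrast would do so with 93% power instead of 74% at the same error rate. The documents do not support this. The ECIG-versus-ECIG pairs compare 8 with 0, 36 with 0 and 36 with 8 mg/ml, so concentration is tested. The NNAL hypothesis in the Aim section is stated relative to the substitute, which a contrast over the ECIG arms leaves out. The two power figures use different alphas. Once the trend is held to the primary error control, it does not beat the planned pairs in any of the four patterns beyond simulation noise.

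**Conclusion.** The point holds as an efficiency gain, not as a flaw in validity. Holm over the same six comparisons raises power for the 36-versus-0 pair from about 74% to 76-79%, at a familywise error of at most 0.05. The range assumes 100 completers per arm, SD 0.6, a 0.28 difference, two-sided testing and a substitute mean equal to the 0 mg/ml mean. The gain is nearer one point when all four arms differ in equal steps. The chance of at least one rejection stays the same. The family is taken as the plan defines it, six comparisons at each analysed time point; Holm does nothing about multiplicity across time points. A concentration trend is at most an optional secondary estimate, and its absence is not a defect.

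**What to change.** In the Statistical analysis section, replace the Bonferroni threshold of 0.008 with this rule: at each analysed time point, a comparison is significant if its Holm-adjusted p-value over the six comparisons is below 0.05. The pairs and the regression model stay as they are.

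The cost is one sentence and a change of adjustment option, made before unblinding. The small downside is that Holm has no simple simultaneous intervals. Report Tukey-Kramer or Bonferroni intervals alongside, and say that an interval may occasionally include zero where Holm rejects.

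Optionally, pre-specify a linear contrast over 0, 8 and 36 mg/ml as a secondary analysis at 0.05, with its slope and 95% CI. State that its power depends on shape (about 93% linear, 88% equal steps, 72% plateau from 8 mg/ml), that most of its apparent gain comes from the looser alpha, and that it does not replace the ECIG-versus-substitute comparisons.

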### Randomization, allocation concealment, and sequence generation

The four conditions are a cigarette substitute that does not produce aerosol, 0 mg/ml nicotine content ECIG (placebo), 8 mg/ml nicotine content ECIG (low), and 36 mg/ml nicotine content ECIG (high). Blocked randomization is accomplished with a 1:1:1:1 ratio of condition assignments at each participating institution with a goal of 260 randomized per site (*N* = 260 for VCU and PSU; *N* = 520 total). The assignment codes are made from separate randomization lists created in advance by the statistician for each site stratum. The randomization lists are stored in a secure, password protected drive and are shared only with unblinded staff. Once a participant has been confirmed eligible for randomization, a computer procedure will assign the participant to the next condition on the list automatically.

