At Visit 2, randomized participants will complete tobacco-related and psychosocial study measures, and biomeasures will be collected. Tobacco-related measures include assessments of dependence, and psychosocial measures include the Kessler 6 [46], Perceived Stress Scale [47], and Center for Epidemiologic Studies-Depression scale [48]. Biomeasures include expired air CO, a pulmonary function test (PFT), exhaled breath condensate collection, and blood and urine samples. Blood samples will be submitted to the VCU/PSU hospital laboratory for a complete metabolic panel, hematology panel, lipid panel, and C-reactive protein assessment. An additional blood sample will be processed and stored for later analysis of oxidative stress markers. Urine samples will be stored for later analysis of cotinine, NNAL, and oxidative stress makers, and exhaled breath condensate will also be stored for later analysis for oxidative stress markers.

At the conclusion of Visit 2 participants will be instructed to start reducing cigarette smoking by 50 % starting the next day. The researcher will discuss with the participant ways to reduce cigarette consumption (e.g., only carrying the allowed number of cigarettes). Participants also will be instructed that they will be expected to complete daily diaries related to their study product and cigarette use. Visit 2 begins the intervention phase (study week 0) and the 50 % reduction phase of the study will continue through Visit 3 (study week 1) and Visit 4 (study week 2), with instructions for 75 % cigarette reduction given at the conclusion of Visit 4. At Visit 5 (study week 4), biomeasures will be completed again excluding hospital laboratory testing of blood sampled.

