### Primary outcome

The primary outcome measure of this RCT is the urinary concentration of the carcinogen biomarker of tobacco exposure, NNAL.

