### Sample size

RCT power is based on the important biomarker of toxicant exposure, NNAL concentration in urine. Unfortunately, there are no data that reveal the NNK exposure in ECIG users, as that study has not yet been performed. However, we do have data showing how NNAL concentration in novel tobacco product users compares to own brand cigarette use [49]. Using these data, power analysis revealed 100 completers per condition would provide an 80 % power to detect an effect size of 0.28 pmol/ml (SD = 0.6 pmol/ml) on NNAL. We aim to enroll 130 participants per condition anticipating a 20 % attrition rate.

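### The primary NNAL regression names neither baseline NNAL nor site, and the adjusted analysis adds covariates by a baseline p < 0.20 screen, so available precision is given up

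*Protocol article*

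**What the plan says.** All references are to the protocol article.

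- **Primary outcome:** "The primary outcome measure of this RCT is the urinary concentration of the carcinogen biomarker of tobacco exposure, NNAL".
- **Statistical analysis, primary model:** NNAL is "summarized by study intervention and time and analyzed using linear regression". The multiplicity correction covers all six contrasts between pairs of arms at a visit, and the threshold is fixed: "p-values less than 0.008 will be considered significant after a Bonferroni multiple comparisons adjustment". No covariate is named for this model.
- **Statistical analysis, adjusted model:** "A secondary analysis will be completed adjusting for age, gender, and race, along with any other covariates that differ across research interventions at baseline". The threshold for those extra covariates is p < 0.20. A repeated measures linear mixed model is a further secondary analysis, with no covariates given. Secondary endpoints follow the same pattern.
- **Randomization section:** "The assignment codes are made from separate randomization lists created in advance by the statistician for each site stratum".
- **Study visits, Visit 2 (study week 0):** "Biomeasures include expired air CO, a pulmonary function test (PFT), exhaled breath condensate collection, and blood and urine samples". The same section says that urine is stored for later NNAL and cotinine assay.
- **Sample size:** 100 completers per condition for 80% power to detect "an effect size of 0.28 pmol/ml (SD = 0.6 pmol/ml) on NNAL". No alpha and no baseline correlation are given there.

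**The concern.** Two choices look wrong.

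First, the primary comparison is a plain between-arm regression at each visit, with adjustment moved to a secondary analysis. In daily smokers, a person's own pre-intervention NNAL is the obvious candidate for the strongest predictor of later NNAL. Leaving it out keeps between-person variation in the residual and widens every confidence interval. Leaving out the stratification factor makes the standard errors slightly too large, because the design has removed between-site imbalance and the analysis takes no credit for it.

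Second, age, gender and race are fixed in advance, but every other covariate must pass a between-arm significance test at baseline. In a randomised trial that test measures chance. A strongly prognostic variable that happens to be balanced is left out, and an irrelevant one that happens to differ is put in. The content of the adjusted model, and so its estimate, depends on which variables happened to differ.

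What is at stake is power for the primary endpoint at a strict threshold, and an adjusted analysis whose form is unknown until baseline data are tested.

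**Working it through.** **Inputs.** Difference 0.28 pmol/ml, SD 0.6 pmol/ml, 100 completers per arm (Sample size). Alpha 0.008 (Statistical analysis), taken as two-sided because the article gives no sidedness. The correlation ρ between baseline and follow-up NNAL is not given, so a range is assumed. The SD of 0.6 is assumed to be the unadjusted SD.

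**Step 1: the article's own figure.** Normal approximation, n per arm = 2[SD(z₁₋α/₂ + z₀.₈₀)/δ]².

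- Two-sided 0.008: 2[0.6(2.652 + 0.842)/0.28]² = 112.1, so 113 per arm. Power at 100 is 74.1%.
- Two-sided 0.05: 73 per arm. Power at 100 is 91.0%.
- Two-sided 0.05/3: 97 per arm. Power at 100 is 81.8%.
- One-sided 0.008: 98 per arm. Power at 100 is 81.4%.

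The stated 100 is matched by the last two readings, neither of which the article states. It is not matched at two-sided 0.008. Every reading that works uses the full SD of 0.6, with no reduction for baseline.

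**Step 2: adding baseline NNAL.** ANCOVA multiplies the residual SD by √(1 − ρ²). Power is taken from the noncentral t with noncentrality δ / [SD·√(1 − ρ²)·√(2/100)] and the variance pooled over four arms (4 × 100 − 4 = 396 df). The one degree of freedom spent on the covariate does not change the figures shown. At ρ = 0 the noncentrality is 0.28/(0.6 × 0.1414) = 3.30, against a critical value of 2.666.

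| ρ (assumed) | SE multiplier | Power at two-sided 0.008 |
|---|---|---|
| 0 | 1.00 | 73.7% |
| 0.1 | 0.99 | 74.2% |
| 0.2 | 0.98 | 75.8% |
| 0.3 | 0.95 | 78.6% |
| 0.34 | 0.94 | 80.0% |
| 0.4 | 0.92 | 82.4% |
| 0.5 | 0.87 | 87.3% |
| 0.6 | 0.80 | 92.7% |
| 0.7 | 0.71 | 97.4% |

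The normal approximation gives slightly higher values (74.1% at ρ = 0, 87.7% at 0.5) and a break-even of 0.33.

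**Step 3: does the gain depend on the unstated alpha?** At two-sided 0.05/3 (normal approximation), power rises from 81.8% to 85.7% (ρ 0.3), 92.2% (0.5) and 98.7% (0.7). The gain is there on either reading.

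**Step 4: site alone.** If site explains 1% to 5% of the variance (assumed), power at two-sided 0.008 moves from 74.1% to between 74.7% and 76.8% (normal approximation).

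**Step 5: the p < 0.20 screen.** Under correct randomisation a baseline p-value is roughly uniform, so each candidate passes with probability 0.20 whatever its prognostic value. Baseline NNAL, if screened at all, enters about one time in five. With 10 independent candidates, 10 × 0.20 = 2 enter by chance on average, and the chance of at least one is 1 − 0.8¹⁰ = 89%. Site, balanced by blocking within site, would essentially never pass.

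**The case against.** **The article never calls the primary model unadjusted, and model terms are often left to the SAP.** The word is indeed absent. But the section sets linear regression against a separate adjusted analysis, which leaves no other natural reading, and it states a specific covariate rule and hierarchy. An SAP that followed this text would inherit both. The argument has most force for site, which the section simply does not mention.

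**Nothing here is biased.** This stands. An unadjusted comparison of randomised arms is valid, omitting site is at most conservative, and the screen governs only a secondary analysis. Chance baseline imbalance is part of the same sampling variance as the wider standard error, not a second harm.

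**The size of the gain rests on assumptions.** This stands as a limit. The correlation is unknown, and the instructed 50% and then 75% cut in cigarettes, followed unevenly, could weaken it. Below about 0.34, adjustment does not bring power to 80% at two-sided 0.008. If the SD of 0.6 is already a change or residual SD, part of the gain is counted twice. Even so, adjustment costs nothing beyond a trivial loss of degrees of freedom.

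**The mixed model may use Visit 2 NNAL.** It may, but the article does not say so, and that analysis is not the primary one.

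**Visit 2 may not be a clean baseline.** The visit description puts the brief trial of ECIG liquids before the biomeasures and does not fix the order of sampling. This needs one clarifying sentence; it does not undo the point.

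**Conclusion.** The concern holds. As written, the primary NNAL model uses neither the baseline value nor the stratification factor, and the adjusted model selects its extra covariates on chance imbalance. The consequence is lost precision and an adjusted analysis of unpredictable content, not bias or an inflated type I error.

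For correlations of 0.4 to 0.7 the standard error falls by 8% to 29%, and power at two-sided 0.008 rises by about 9 to 24 percentage points; at 0.2 the gain is about 2 points. These figures assume that the SD of 0.6 is unadjusted. The gain from site is probably small, and the main reason to include it is that the analysis should match the randomisation.

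That the change is worth making is well supported; how large the gain will be is not known from the document. It should be made before the data are analysed.

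**What to change.** 1. **Primary model.** At each time point, fit NNAL on the analysis scale by ANCOVA with terms for arm, Visit 2 NNAL on the same scale, and site. Keep the six pairwise contrasts and their threshold.
2. **Secondary endpoints.** Use the same form, each with its own baseline value and site.
3. **Secondary adjusted analysis.** Delete the p < 0.20 rule. Fix the list in advance: baseline value, site, age, gender, race and baseline cigarettes per day. The last of these is a suggestion; any list chosen beforehand for prognostic value would do.
4. **Baseline definition.** State whether the Visit 2 samples are taken before or after participants try the study product.

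The cost is analysis wording only. Visit 2 urine, site, demographics and the baseline-week cigarette diary are already collected, so no participants, visits or assays are added.

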The continuation phase of the study is from Visit 6 (study week 8), Visit 7 (study week 12), Visit 8 (study week 16), Visit 9 (study week 20), through Visit 10 (study week 24). At each visit, participants will complete appropriate study measures and will be instructed to continue to reduce their cigarette consumption. At Visit 7 and Visit 10, biomeasures will be completed, but hospital laboratory testing of blood is only completed at Visit 10. At the conclusion of Visit 10, study product supplies will cease as well as use of the daily diary. Participants will be advised to cease all cigarette use and provided with freely available evidence-based smoking cessation resources. Those participants who were randomized to the cigarette substitute condition will be eligible to receive an ECIG with one week’s worth of cartomizers at 0 mg/ml; those randomized to an ECIG condition will be eligible to receive a cigarette substitute. This procedure, outlined during the consent process, is designed to increase the likelihood of retention for any participants who may have joined the study to reduce their cigarette consumption with an ECIG but were randomized to receive the cigarette substitute. Participants return during the follow-up phase at Visit 11 (study week 28) and Visit 12 (study week 36). Please note at each visit following consent, adverse events/medication changes and study product side effects (among other study measures) are assessed, and a 7-day TLFB is administered to assess cigarette and study product use. Participant compensation consists of $20 gift cards at each visit attended and an additional $20 gift card at visits where biomeasures are obtained; a bonus of $80 is given at the conclusion of the Visit 12 for those who complete all study visits.

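### The six-comparison Bonferroni threshold of 0.008 holds type I error below 5% only within a visit, while NNAL is measured at three post-baseline visits and the text ranks none of them

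*Protocol article*

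**What the plan says.** The Primary outcome section gives a variable but no visit: "The primary outcome measure of this RCT is the urinary concentration of the carcinogen biomarker of tobacco exposure, NNAL".

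The Study visits section puts urine among the biomeasures: "Biomeasures include expired air CO, a pulmonary function test (PFT), exhaled breath condensate collection, and blood and urine samples". It says that the urine is stored for NNAL, among other assays. Biomeasures are taken at Visit 2 (week 0) and then three times after baseline. The first is week 4: "At Visit 5 (study week 4), biomeasures will be completed again". The other two are weeks 12 and 24: "At Visit 7 and Visit 10, biomeasures will be completed". No biomeasures are stated for the follow-up visits (Visits 11 and 12).

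The Statistical analysis section sets a general rule, "P-values less than 0.05 will be considered statistically significant", and excepts the primary analysis, "where p-values less than 0.008 will be considered significant after a Bonferroni multiple comparisons adjustment". It lists the contrasts: "We will compare each ECIG group to the cigarette substitute and then each ECIG group to the other". It fixes the scope of the correction: "we will adjust the Type I error rate to account for 6 pairwise comparisons at each time point". The repeated measures mixed model, which could have combined the visits, appears only among the secondary analyses.

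**The concern.** The correction accounts for the number of pairs of arms but not for the number of visits. Dividing 0.05 by six spends the whole 5% at one visit, and the same 5% is spent again at each of the other two.

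The Statistical analysis section states one primary objective, the influence of nicotine concentration on NNK exposure, and does not tie it to a visit. As written, a difference at week 4, 12 or 24 could each be presented as the primary finding, and the choice could be made after the results are seen. At stake are the chance of a false primary claim and the clarity about which visit carries the conclusion.

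**Working it through.** **Inputs from the article.** Four arms, allocated 1:1:1:1. Threshold 0.008. Six pairwise comparisons per time point. Three post-baseline NNAL visits (weeks 4, 12, 24). For power: 100 completers per arm, difference 0.28 pmol/ml, SD 0.6 pmol/ml.

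**Assumptions.** Two-sided tests (the article does not say). The between-visit correlation of NNAL (rho) is not given, so a range is shown, with the same rho for every pair of visits. Baseline is not counted as a test.

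**1. The plan's own figure.** Three ECIG arms against the substitute plus three ECIG pairs make 6 comparisons. 0.05 / 6 = 0.00833, which is 0.008 to three decimals. The figure reproduces, rounded slightly to the safe side.

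**2. One visit.** Six correlated pairwise z-tests at 0.008 under the global null (four equal arms, 2,000,000 simulated replicates) give a familywise error of 4.0%. The correction works within a visit.

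**3. Three visits.** Number of tests: 3 x 6 = 18.

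- Bonferroni bound: 18 x 0.008 = 0.144, or 14.4%.
- Uncorrelated visits: 1 - (1 - 0.040)^3 = 0.115, or 11.5%. The simulation gives the same figure.
- Correlated visits, by simulation, counting any significant pair at any visit:

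| Assumed rho | Familywise error | Relative to 5% |
|---|---|---|
| 0 | 11.5% | 2.3 |
| 0.5 | 10.5% | 2.1 |
| 0.7 | 9.3% | 1.9 |
| 0.8 | 8.3% | 1.7 |
| 0.9 | 7.0% | 1.4 |
| 0.95 | 6.2% | 1.2 |
| 0.99 | 5.0% | 1.0 |

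The rate stays above 5% for every correlation below about 0.99.

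**4. Two ways to restore control.**

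- *One primary visit, six tests at 0.008:* familywise error 4.0% (step 2), with the stated threshold unchanged.
- *All three visits kept primary:* 0.05 / 18 = 0.0028 per test. Familywise error is then 4.4% at rho 0 and 2.8% at rho 0.9.

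Power by the normal approximation is Phi(delta / (SD x sqrt(2/n)) - z). Here 0.28 / (0.6 x sqrt(2/100)) = 3.30.

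- At 0.008, z = 2.652 and power is Phi(0.65), about 74%.
- At 0.05/18, z = 2.991 and power is Phi(0.31), about 62%.
- 80% power at 0.05/18 needs 135 completers per arm, more than the 130 per arm to be enrolled.

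The right starting point for this comparison is 74%, not the 80% in the Sample size section. The gap between those two figures is a separate matter on which this point does not depend.

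**The case against.** The strongest reply is that the plan does what it says. It promises correction for six comparisons per time point, and at 4.0% it delivers that. A reader might infer that a declared 5% guarantee over the whole primary family is broken. The article declares no such guarantee: it mentions neither familywise nor trial-wide error. The criticism is that the chosen scope is too narrow.

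A reader might also infer that one significant result among the 18 would count as success. The article states no success rule of that kind. The 6% to 11% figures apply if the results are read that way; the text leaves that reading open but does not prescribe it.

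Third, the article condenses a fuller protocol, and an SAP may name the primary visit. That is fair, and a missing time point alone would be no finding. But the article does more than stay silent. It fixes a threshold for the primary analysis and says that the correction applies at each time point. An SAP naming one visit would have to narrow that rule.

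Finally, it can be argued that each visit asks its own question, so that per-visit control suffices. The single primary objective and the NNAL hypothesis in the Aim section are not specific to a visit, which weakens this argument.

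**Conclusion.** The point holds as a defect in a stated rule. The 0.008 threshold controls error within a visit (4.0%) but not across the three visits at which the primary variable is measured, and nothing in the text ranks those visits. If significance at any visit may be read as meeting the primary objective, familywise error under the global null is about 6% (assumed correlation 0.95) to 11% (correlation 0), with an upper bound of 14.4%. Zero correlation between repeated samples from the same smokers is an extreme case, so the upper end should not be taken as the expected value. The direction does not depend on the correlation unless it reaches about 0.99.

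**What to change.** In Primary outcome and Statistical analysis, name one primary time point for NNAL. Week 24 (Visit 10) is the natural choice because it closes the 24-week intervention, although the article itself does not rank the visits. Apply the six comparisons at 0.008 to that visit, and make weeks 4 and 12 secondary. If the SAP already names a primary visit, the wording in Statistical analysis should be brought into line with it.

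The change takes a sentence or so and needs no new data. It keeps the 0.008 threshold and the planned sample. The small downside is that differences at the earlier visits can no longer be claimed as primary results.

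Spreading Bonferroni over all 18 tests is not recommended. At 100 completers per arm it lowers two-sided power from about 74% to about 62%. An ordered testing of visits, or making the planned mixed model primary with a prespecified contrast, could also control the error but would change the plan more.
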